#### Treatment Arm 2: HIV Self-Testing Plus mHealth

Participants in this arm will be enrolled into the HIV self-testing group (as above) and on a web-based SMS platform hosted by WelTel [40,41]. WelTel is a nonprofit agency developing the mHealth intervention, in which participants receive weekly supportive bidirectional text messages asking how they are doing [42]. Participants are requested to reply “fine” or “not fine,” and those responding “not fine” will be contacted with support by a peer navigator. Participants in this arm will discuss the weekly WelTel messages with peer navigators and respond to the “not fine” messages within 2 days. If they do not reply to the initial SMS message within the specified timeframe, a peer navigator will follow up with them during that week. The WelTel system will manage the SMS intervention on a structured mobile phone platform (all SMS interactions are logged). WelTel’s two-way texting mHealth intervention may prompt participants to engage in HIV self-testing and/or to engage peer navigator support in decision making regarding HIV self-testing practices.

#### Arm 3: Standard of Care

Participants in this arm will be enrolled into a standard of care group. Participants will receive information about HIV testing, care, and support services at local clinics. They will be provided a pamphlet of information about HIV and HIV prevention strategies (written in French, English, Luganda, Kirundi, Kinyarwanda, and Swahili).

### Outcomes

#### Primary Outcomes

The primary outcomes measured in this trial are as follows:

Changes in HIV testing frequency: This is measured as participants’ self-reported last HIV test. To capture changes, this measure is assessed at all three study time points (baseline [Time 1], 8 months [Time 2], and 12 months [Time 3]).Changes in knowledge of HIV status: To address social desirability bias challenges regarding self-reported HIV serostatus, multiple steps are employed. First, at each timepoint (Time 1, Time 2, and Time 3), participants are asked their current HIV status. At Time 3, participants are offered a completely voluntary rapid HIV test. Knowledge of HIV status will be assessed as correct for persons who agree to take the rapid test and correctly report their HIV status (prior to receiving the result).Changes in linkage to confirmatory HIV testing: Participants in trial arms 1 and 2 (HIV self-testing and mHealth HIV self-testing intervention) are asked at Time 2 and Time 3 if they used their HIV self-testing kit. For those who respond affirmatively, they will be asked the result, and those who report a positive result will be asked if and where they received confirmatory testing.Changes in linkage to HIV care: Participants who seroconvert during the study are asked the frequency of accessing HIV care service since diagnosis. This will be assessed at Time 2 and Time 3.HIV self-testing kit use: To understand the frequency of HIV self-testing kit use and to reduce social desirability bias regarding HIV self-testing kit use, participants in trial arms 1 and 2 will be followed up 1 month after Time 3 to request for purchasing unused kits back. Participants will not be informed of this as an option prior to this time.

#### Secondary Outcomes

Secondary outcomes include changes in depression assessed using the Patient Health Questionnaire-9 items (PHQ-9) [43]; condom use self-efficacy measured with the Condom Use Efficacy Scale [44,45]; consistent condom use frequency assessed by asking participants if they used condoms every time (consistently) in the past 3 months; sexual relationship power assessed using the relationship control subscale from the Sexual and Reproductive Power Scale [46]; perceived HIV-related stigma with the perceived HIV-related stigma subscale of Steward et al [47]; and adolescent SRH stigma assessed with the Ugandan Adolescent SRH Stigma Scale [48] adapted from the Adolescent SRH scale by Hall et al [49].

### Sample Size and Power Analysis

Cluster sizes of 130 per group (n=390) are required to have 80% power (*P*<.05) to detect a 25% difference (39% [5] vs 64% tested) in HIV testing between any two groups from three pairwise comparisons (control vs arm 1, control vs arm 2, and arm 1 vs arm 2) for an odds ratio of 1.66. We assume an intraclass correlation coefficient of 0.013 based on HIV research on condom use in sub-Saharan Africa [50]. With 10% attrition, 432 participants (144 per cluster) are required. Computations were performed using RStudio version 3.3.0 (RStudio Team), based on formulae for multiple comparisons of proportions, and adjusted for design effect [51].

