### Study Design

To evaluate the intervention effectiveness, we will conduct a cluster randomized controlled trial (cRCT), where informal settlements are randomized. The clusters include five informal settlements grouped into three sites that are randomized in a 1:1:1 method to one of three study arms. Although outcome data will be collected at the level of the individual, we selected cluster randomization over individual randomization because the intervention is implemented at the settlement level. A cluster randomized design addresses threats of internal validity. It reduces the possibility of experimental contamination due to the shared social and physical environments between youth in the same or nearby informal settlements [35]. Data will be collected at the following three time points: baseline enrollment into the intervention, 8 months after enrollment, and 12 months after enrollment.

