### Data Analysis Plan

Analysis and reporting will be conducted in accordance with CONSORT (Consolidated Standards of Reporting Trials) guidelines [52] (Multimedia Appendix 1). The analyst will be blinded to group allocation. A flow diagram will be used to illustrate patient flow (screening, randomization, allocation, and follow-up). Baseline data will be reported for all three arms and summarized as mean (SD) or median (first quartile, third quartile) for continuous variables and as count and number (percentage) for categorical variables. Primary analysis will involve intention-to-treat analysis (data from participants will be analyzed according to their allocation, irrespective of whether they actually received that intervention). Between-group comparisons will be performed using multilevel mixed effect logistic or linear regression models (to account for clustering), depending on which outcome is being evaluated. For these models, the intervention group will be entered as a fixed effect. The level of significance will be set at α=.05, but adjusted using the Bonferroni method for secondary outcomes [53]. The results will be expressed as odds ratios or mean differences as appropriate, accompanied by 95% CIs and *P* values. We will conduct adjusted analysis for the primary outcome (changes in HIV testing frequency) to investigate the role of various covariates in the relative effect. We will build mixed effect multilevel logistic regression models with the intervention group as the independent variable and HIV testing uptake in the past 3 months (yes/no) as the dependent variable. Covariates (eg, age) will be entered as a block. We will explore gender differences in primary and secondary intervention outcomes.

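### The stated 80% power with 130 per group does not hold under a two-sided test or any Bonferroni adjustment for three comparisons; two-sided power is 70-72% at 0.05 and 53-56% at 0.05/3

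*Protocol article*

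**What the plan says.** All references are to the protocol article.

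- **Sample Size and Power Analysis** states "Cluster sizes of 130 per group (n=390) are required to have 80% power", at P<.05, "to detect a 25% difference (39% [5] vs 64% tested) in HIV testing". The claim covers any two of the three arms, with all three pairwise comparisons listed, and the effect is labelled an odds ratio of 1.66. On clustering: "We assume an intraclass correlation coefficient of 0.013". On method, the computation was "based on formulae for multiple comparisons of proportions, and adjusted for design effect". Allowing for 10% attrition gives 144 per cluster, 432 in all.
- **Study Design**: "The clusters include five informal settlements grouped into three sites that are randomized in a 1:1:1 method to one of three study arms". With three sites and three arms, each arm is one site. The per-cluster counts in Study Population and Eligibility Criteria (144) and in the abstract (150) also equate arm with cluster.
- **Data Analysis Plan**: "The level of significance will be set at α=.05, but adjusted using the Bonferroni method for secondary outcomes". Results are to be "accompanied by 95% CIs and" P values. No section says whether tests are one-sided or two-sided.

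**The concern.** The section gives every input except sidedness and the exact per-comparison alpha, so its power figure can be checked. With a whole arm in one cluster, even a small ICC inflates the variance considerably: 0.013 across 130 participants reduces them to fewer than 50 effective observations. A 25-point difference is large, but 80% power from fewer than 50 per arm looks too high for a two-sided test, and more so with a correction for three comparisons.

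The stake is interpretation. A reader who trusts the 80% would take a null pairwise comparison on HIV testing as fairly strong evidence against a 25-point effect. If power is between about one half and 72%, a null result says much less.

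**Working it through.** **Inputs.** p1 = 0.39, p2 = 0.64, d = 0.25, ICC ρ = 0.013, m = 130 per group, 80% power and three pairwise comparisons (Sample Size and Power Analysis). One cluster per arm (Study Design). Alpha 0.05 (Data Analysis Plan). Sidedness is not stated, so both are run. Alpha 0.05/3 = 0.0167 is the Bonferroni value for three comparisons.

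**Design effect.** DE = 1 + (m − 1)ρ = 1 + 129 × 0.013 = 2.677. Effective size n = 130/2.677 = 48.6 per arm.

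**Power formulas.** v = 0.39 × 0.61 + 0.64 × 0.36 = 0.4683, √v = 0.684. Mean rate 0.515, so 2 × 0.515 × 0.485 = 0.4996, square root 0.707. d√n = 0.25 × 6.969 = 1.742.

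- Unpooled: Φ(d√n/√v − z) = Φ(2.546 − z)
- Pooled: Φ((1.742 − 0.707z)/0.684)

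**Reproducing the stated figure.** One-sided 0.05, no adjustment (z = 1.645): pooled 80.2%, unpooled 81.6%. In the other direction, the pooled formula needs 48.4 effective per arm, and 48.4 × 2.677 = 129.5, that is 130. So 130 can be recovered with the stated ICC and cluster size, but only on this reading among those below.

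**Power at 130 per arm**

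| Test | z | Pooled | Unpooled |
|---|---|---|---|
| One-sided 0.05 | 1.645 | 80.2% | 81.6% |
| Two-sided 0.05 | 1.960 | 69.9% | 72.1% |
| One-sided 0.05/3 | 2.128 | 63.6% | 66.2% |
| Two-sided 0.05/3 | 2.394 | 52.9% | 56.0% |

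Using 144 per arm instead (the enrolment target, with no attrition) gives 72-74% at two-sided 0.05 and 55-58% at two-sided 0.05/3.

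**Cluster size needed for 80%.** With one cluster per arm the design effect grows with the arm. If N effective participants are needed, m = N(1 − ρ)/(1 − Nρ).

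- Two-sided 0.05: N = 58.8 (unpooled) or 61.5 (pooled). Then m = 58.8 × 0.987/(1 − 58.8 × 0.013), about 247, and about 304 for the pooled value.
- Two-sided 0.05/3: N = 78.4 or 82.3. Effective size can never exceed 1/ρ = 1/0.013 = 76.9, so no m suffices. At that limit power is 76.8% (pooled) to 79.1% (unpooled).
- One-sided 0.05/3: 80% is reached at about 463 (unpooled) to 683 (pooled).

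**Detectable difference.** Solving the same formulas at n = 48.6 for the p2 that gives 80% two-sided power from p1 = 0.39 yields about 27-28 points at 0.05 and 31-32 points at 0.05/3.

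**Odds ratio.** (0.64/0.36)/(0.39/0.61) = 1.778/0.639 = 2.78. The risk ratio is 0.64/0.39 = 1.64. Starting from 39%, an odds ratio of 1.66 would give odds of 0.639 × 1.66 = 1.061, a rate of 51.5%, which is not 64%.

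**Attrition.** 130/0.9 = 144.4, so the 144 is consistent and is not at issue.

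**The case against.** **The figure can be recovered.** A one-sided, unadjusted 0.05 test with exactly the stated ICC and cluster size gives 80-82%, and the article never states sidedness. A reader might infer that 80% cannot come from the stated inputs at all; that goes too far. But this reading does not rescue the section. No one-sided test is declared. The section says that multiple-comparison formulae were used, and one-sided 0.05/3 gives only 64-66%. Reporting 95% CIs fits a two-sided 5% test. A one-sided test also fits poorly with a claim about any two groups, which includes the two self-testing arms.

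**The plan may not adjust the primary outcome.** The Data Analysis Plan names Bonferroni for secondary outcomes only. This stands: 53-56% and the ceiling apply only if the sample-size method used 0.05/3, and the formula source is not at hand. At two-sided 0.05 the shortfall is milder, 70-72% against 80%, with the detectable difference moving from 25 to 27-28 points.

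**No trial size would do.** A reader might infer this from the ceiling. It holds only at two-sided 0.05/3, and narrowly.

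**The settlements could be the clusters.** With five clusters averaging 390/5 = 78 (an assumption; DE 2.00), two-sided power would be 82-84% at 0.05 but 68-71% at 0.05/3. The article, however, randomizes sites and counts 144 per cluster.

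**Two further inferences are unsupported.** One is that the requirement is the unclustered size times 2.677. That fixes the design effect at 130 while the arm grows, and so understates the need. The other is that 1.66 is a misplaced design effect. The article calls it an odds ratio, and nothing in it shows where the number came from.

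**Conclusion.** The concern holds in a conditional form. With one site of 130 per arm and ICC 0.013, the stated 80% is not met by a two-sided test, nor by any Bonferroni adjustment for three comparisons, one-sided or two-sided. Two-sided power is 70-72% at 0.05 and 53-56% at 0.05/3, the ranges spanning the pooled and unpooled formulas. The 80% therefore rests on an undeclared one-sided, unadjusted test, or it is wrong; the text needs correcting either way. Separately, and without any assumption about alpha or clustering, the odds ratio of 1.66 does not match 39% versus 64%.

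These results rest on the site being the cluster, on normal approximations, and on treating 0.013 as known. The last assumption flatters the design: with one cluster per arm, between-cluster variation cannot be separated from the arm effect, so the recomputed powers are themselves optimistic.

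**What to change.** Restate Sample Size and Power Analysis so that it:

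1. states the alpha and sidedness used, and whether three comparisons are adjusted for, consistently with the Data Analysis Plan;
2. gives the design effect of 2.68 for one cluster of 130 per arm;
3. reports power for 39% versus 64% of about 70-72% (two-sided 0.05) or 53-56% (two-sided 0.05/3), with detectable differences of about 27-28 or 31-32 points; if a one-sided, unadjusted test was intended, says so and reconciles it with the multiple-comparison wording and the 95% CIs;
4. replaces the odds ratio of 1.66 with 2.78 (risk ratio 1.64);
5. says that these figures treat the ICC as known and are optimistic, because with one cluster per arm between-cluster variation cannot be separated from the arm effect.

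The cost is a change of text and a less favourable published power. Recruitment is already complete at 452, and no extra enrolment is proposed.

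### The odds ratio of 1.66 attached to the target effect is wrong: 39% versus 64% tested is an odds ratio of 2.78

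*Protocol article*

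**What the plan says.** The Sample Size and Power Analysis section of the protocol article sets the target as "detect a 25% difference (39% [5] vs 64% tested) in HIV testing" and, later in the same sentence, puts it on a second scale: "for an odds ratio of 1.66". The power is 80% at a 0.05 level with sidedness not stated, for "Cluster sizes of 130 per group (n=390" in total before attrition. The section also says "We assume an intraclass correlation coefficient of 0.013", and that the computation used formulae for several comparisons of proportions with a design-effect adjustment.

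The Data Analysis Plan specifies mixed-effect logistic models for binary outcomes and says: "The results will be expressed as odds ratios or mean differences as appropriate". Nowhere does the article give 1.66 another meaning or pair it with another control rate.

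**The concern.** One sentence describes one target in two ways, and the two do not agree. The proportions describe a large effect. The odds ratio describes one about half as large on the log scale.

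The odds ratio is also the only design figure given on the scale on which the main binary comparisons will be reported. A reader who sets the trial's estimates beside 1.66 would believe that the trial had 80% power for an effect of that size. A non-significant result could then be taken as evidence against modest effects that the trial had little chance of detecting.

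**Working it through.** **Inputs** (Sample Size and Power Analysis): p1 = 0.39, p2 = 0.64, stated odds ratio 1.66, 130 per group, 80% power, alpha 0.05. Two-sided testing is my assumption unless stated otherwise.

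**1. Can 1.66 be reproduced as an odds ratio?**
- OR = [p2/(1 − p2)] / [p1/(1 − p1)] = (0.64/0.36)/(0.39/0.61) = 1.778/0.639 = 2.78.
- If both percentages were rounded to whole numbers, the range is 2.66 (0.395 vs 0.635) to 2.90 (0.385 vs 0.645).
- A cluster-specific odds ratio from a mixed model at an intraclass correlation of 0.013 is about 2.80, which is further from 1.66.
- Another control rate does not help. For a fixed 25-point difference the odds ratio is smallest when the two rates lie symmetrically about 50%: (0.625/0.375)² = 2.78. No 25-point difference has an odds ratio of 1.66.

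So 1.66 is not reproduced.

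**2. What 1.66 would mean as an odds ratio from 39%**
- p2 = (0.39 × 1.66)/(0.61 + 0.39 × 1.66) = 0.6474/1.2574 = 0.515, a difference of 12.5 points.
- Log scale: ln 1.66 = 0.507 and ln 2.78 = 1.023; the ratio is 0.50.

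**3. Power of 130 per group for that effect, clustering ignored**
- Standard error = √[(0.39 × 0.61 + 0.515 × 0.485)/130] = √(0.4877/130) = 0.0612.
- Power = Φ(0.1249/0.0612 − 1.96) = Φ(0.08) = 53%.
- Any design effect above 1 lowers this.

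**4. Did 1.66 drive the sample size?**
- 80% power for an odds ratio of 1.66 from 39% needs 249 per group (pooled two-proportion formula, two-sided 0.05) before any design effect, or 332 at 0.05/3.
- Even one-sided at 0.05, the log-odds-ratio formula gives (1.645 + 0.842)² × (1/0.2379 + 1/0.2498)/0.507² ≈ 198 per group before any design effect.
- The stated 130 already includes a design effect, so it cannot come from 1.66.
- For 39% versus 64%, the unpooled formula gives (1.960 + 0.842)² × (0.2379 + 0.2304)/0.25² = 58.8 per group at two-sided 0.05, and 78.4 at 0.05/3. A figure of 130 after inflation is compatible with this target.

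**5. Candidates for what 1.66 is**
- Risk ratio: 64/39 = 1.64, with a rounding range of 1.61 (0.635/0.395) to 1.675 (0.645/0.385). That range includes 1.66.
- Design effect: 130/78.4 = 1.66. This needs the unpooled formula and two-sided alpha of 0.05/3, neither of which the article states.
- The 130 can also be reached without 1.66: the pooled formula at one-sided 0.05 gives 49, and 49 × [1 + 129 × 0.013] = 49 × 2.677 = 131.

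The article does not allow a choice among these.

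**The case against.** The strongest reply is that nothing in the trial depends on the wrong figure. The target is fixed by two explicit proportions, the method is described as one for proportions, and 130 per group fits those proportions. The Data Analysis Plan does not use 1.66 as a margin, threshold or model input. Recruitment is complete at 452, and correcting the label changes no estimate or test. All of this stands, and it limits the severity. It does not remove the error: the figure is stated as fact inside the power claim, on the reporting scale, and a statistical analysis plan that is not shown could not make it right.

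A reader might infer more than the article supports, in two ways.

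- **That the trial was sized for an odds ratio of 1.66 and is therefore underpowered.** Step 4 points the other way. The 53% measures the gap between the two stated effects. It is not the trial's power for 39% versus 64%.
- **That 1.66 is a mislabelled design effect.** The match of 130/78.4 is suggestive, but it rests on unstated choices, and a rounded risk ratio fits as well. If it were the design effect, replacing it with 2.68 for clusters of 130 would give 78.4 × 2.68 ≈ 210 per group. That would change the sample size, so it is a separate question and cannot be settled as part of a label correction.

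**Conclusion.** The stated odds ratio is wrong. The proportions in the same sentence give 2.78 (2.66 to 2.90 under rounding), and 1.66 is about half of that on the log scale. The 80% power claim does not extend to an odds ratio of 1.66, for which 130 per group gives about 53% before clustering.

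The odds ratio of 2.78 follows from the article's own figures without further assumptions. The 53% assumes two-sided 0.05, a control rate of 39%, a normal approximation and no clustering. The view that the sample size rests on the proportions is an inference from the size of 130, but a firm one, since every calculation above for 1.66 needs well over 130.

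This is a moderate reporting correction. Whether the design effect actually used agrees with an intraclass correlation of 0.013 and clusters of 130 is a separate sample-size question, which this point does not decide.

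**What to change.** In Sample Size and Power Analysis, express the target as: 39% vs 64%, a 25 percentage-point difference, odds ratio 2.78 (risk ratio 1.64). If 1.66 is another quantity, such as a risk ratio or a design effect, keep it only under its correct name.

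The cost is one line of text, with no change to the analysis or to the number enrolled. If the sponsor finds that 1.66 was the design effect, the sample-size calculation should be taken up as a matter of its own and not folded into this edit.

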### Data Collection and Management

Outcome data will be collected at three time points as identified using a tablet-based survey application (QuickTapSurvey, Formstack for Time 1; SurveyCTO, Dobility for Time 2 and Time 3). Baseline data to characterize the study population include demographics and sexual history, which will be collected using these tools. Data will be automatically uploaded onto a secure password-protected server using an SSL certificate and will remain encrypted when not in use.

### Data Analysis Plan

Analysis and reporting will be conducted in accordance with CONSORT (Consolidated Standards of Reporting Trials) guidelines [52] (Multimedia Appendix 1). The analyst will be blinded to group allocation. A flow diagram will be used to illustrate patient flow (screening, randomization, allocation, and follow-up). Baseline data will be reported for all three arms and summarized as mean (SD) or median (first quartile, third quartile) for continuous variables and as count and number (percentage) for categorical variables. Primary analysis will involve intention-to-treat analysis (data from participants will be analyzed according to their allocation, irrespective of whether they actually received that intervention). Between-group comparisons will be performed using multilevel mixed effect logistic or linear regression models (to account for clustering), depending on which outcome is being evaluated. For these models, the intervention group will be entered as a fixed effect. The level of significance will be set at α=.05, but adjusted using the Bonferroni method for secondary outcomes [53]. The results will be expressed as odds ratios or mean differences as appropriate, accompanied by 95% CIs and *P* values. We will conduct adjusted analysis for the primary outcome (changes in HIV testing frequency) to investigate the role of various covariates in the relative effect. We will build mixed effect multilevel logistic regression models with the intervention group as the independent variable and HIV testing uptake in the past 3 months (yes/no) as the dependent variable. Covariates (eg, age) will be entered as a block. We will explore gender differences in primary and secondary intervention outcomes.

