### Study Setting

This trial is being conducted in Kampala, which is the capital of Uganda. Uganda’s progressive refugee policies provide refugees and displaced persons in refugee settlements a plot of land. Yet, with the 2006 Uganda Refugee Law, refugees forgo rights to humanitarian assistance if they leave these refugee settlements [16,17]. The convergence of this law with refugee urbanization contributes to extreme poverty among Kampala’s urban refugees, creating slum environments [16,36,37]. Among Ugandan youth aged 15 to 19 years, the HIV prevalence is estimated at 4% [38]. However, among vulnerable youth living in Kampala’s informal settlements, this is estimated at 37.2% [39]. The five informal settlements selected for this study are grouped into three sites based on their proximity to one another (Kabalagala/Kansanga, Katwe/Nsambya, and Rubaga) and have been purposively chosen because these communities host many displaced/refugee persons in Kampala [16,18,36,37]. We focused on these refugee communities, largely from the Democratic Republic of Congo, Rwanda, and Burundi [13], where refugees continue to arrive, owing to similarities in socioeconomic status and living conditions, health care access, and shared languages (French and Swahili).

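### The unqualified claim of a blinded analyst cannot hold for the comparisons with standard of care once the kit and confirmatory-testing outcomes are in the analysis file

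*Protocol article*

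**What the plan says.** The Data Analysis Plan states: "The analyst will be blinded to group allocation". It names no outcome, comparison or stage to which this is limited, and it is the only blinding statement in the article. The same section puts arm into multilevel models: "For these models, the intervention group will be entered as a fixed effect".

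Under Primary Outcomes, two of the five listed items are confined to the self-testing arms. For linkage to confirmatory testing, participants in arms 1 and 2 "are asked at Time 2 and Time 3 if they used their HIV self-testing kit", then what the result was and, if positive, whether and where it was confirmed. For kit use, "participants in trial arms 1 and 2 will be followed up 1 month after Time 3 to request for purchasing unused kits back".

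Two design features also matter. Study Design says: "The clusters include five informal settlements grouped into three sites that are randomized in a 1:1:1 method to one of three study arms". Study Setting gives the sites as "Kabalagala/Kansanga, Katwe/Nsambya, and Rubaga". For arm 2 only, the text-message platform keeps a record: "all SMS interactions are logged".

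**The concern.** Coding the arms as A, B and C masks an analyst only if nothing else in the file shows which code is which. Here some primary outcomes exist in two arms and cannot exist in the third, because standard-of-care participants receive no kit. The outcome list therefore conflicts with the blinding sentence. This is not a complaint about missing detail: no separate analysis plan can create kit data in a group without kits.

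The stake is the credit readers give to the analysis. Participants know whether they were given a kit, and the outcomes are largely self-reported, so analyst blinding is the only masking the article claims. The testing-frequency analysis leaves some choices open in the article: covariates are given only by example (age), gender differences are to be explored, and the outcome is the self-reported last test under Primary Outcomes but a yes/no for the past three months in the Data Analysis Plan. A reader of the trial report would assume that such choices were made without knowing which group was the control.

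**Working it through.** The article gives no figure for this point, so the check is one of logic: which arms does each item tell apart, and how many labellings of three coded groups survive?

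**Inputs, by section**

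- Testing frequency (Primary Outcomes): all three time points, not described as arm-specific. Separates no arms.
- Knowledge of HIV status (Primary Outcomes): status asked at each time point, voluntary rapid test at Time 3, not described as arm-specific. Separates no arms.
- Linkage to confirmatory testing, with kit use and self-test result (Primary Outcomes): arms 1 and 2 only. Separates arm 3 from the other two.
- Linkage to HIV care (Primary Outcomes): participants who seroconvert, not tied to an arm there. Not counted as revealing.
- Kit buy-back (Primary Outcomes): arms 1 and 2 only. Separates arm 3 from the other two.
- Six secondary outcomes (Secondary Outcomes): not described as arm-specific. Separate no arms.
- SMS logs (Treatment Arm 2): arm 2 only, held on the messaging platform. They are not named as an outcome or a model variable.
- Site or settlement (Study Design, Study Setting): three sites, one per arm.

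**Count of labellings**

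1. Three coded groups can be matched to three arms in 3! = 3 × 2 × 1 = 6 ways.
2. With the kit and confirmatory-testing fields in the file, exactly one group has them empty for every participant. Missed visits cannot mimic this, since they would blank some records in a self-testing arm but not all. That group is arm 3, so 2! = 2 labellings remain.
3. The chance of naming the control group correctly rises from 1/3 to 1. The chance of naming all three correctly rises from 1/6 to 1/2.
4. The Sample Size section lists three pairwise comparisons. Control versus arm 1 and control versus arm 2 both involve the identified group, so for both the analyst knows which side is control: 2 of 3.
5. Arm 1 versus arm 2: both arms have the same kit, result, confirmatory-testing and buy-back fields. No listed outcome tells them apart, so the last 2 labellings stay open.

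**What the site structure adds**

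With one site per arm, a coded site variable gives the same three-way split as the arm code, and so adds nothing about which group is which. The sites contain 2, 2 and 1 settlements, so even coded settlement identifiers let an analyst recognise the one-settlement site as Rubaga. That reveals an arm only to someone who knows which arm Rubaga received, which the article does not state. The masking is fragile here, but not broken.

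**How likely the exposure is**

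Data Collection and Management describes a single survey application for Time 2 and Time 3, and the kit questions are asked at those visits. Unless fields are deliberately held back, an extract containing testing frequency also contains the kit items. Buy-back is a separate contact after Time 3, planned for June 2021 according to Results.

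**The case against.** A reader might infer that every arm is revealed and that the trial has no analyst blinding at all. The documents do not support this, for three reasons.

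- The SMS logs would identify arm 2, but no outcome or model uses them and nothing says they reach the analyst.
- Site identifies arm only with the site-to-arm key, which the article neither gives nor says the analyst holds.
- Kit use and confirmatory testing can still be compared between arms 1 and 2 on coded groups, so it is not true that they cannot be analysed blind in any sense.

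It can also be said that this is a journal article: who holds the key, how extracts are split and when unblinding occurs are usually set out in a fuller document, and nothing states that the analyst receives one merged file. Covariates and missing-data handling may likewise be fixed in an analysis plan not shown, and the three-month window is stated. All of this stands. The absence of a procedure is not held against the article, no weight is put on missing-data handling, and no bias in any estimate is shown.

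What the objection does not remove is the conflict between an unqualified sentence and a list of primary outcomes that singles out the control group. A split of extracts could protect the common outcomes. It could not make the sentence true for a file that holds the arm-specific ones.

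**Conclusion.** The point holds in limited form. As written, the blinding claim is wider than the design can support. Once the kit, self-test, confirmatory-testing or buy-back fields are in the analysis file, standard of care is identified with certainty and 2 of the 3 pairwise comparisons are unmasked. The comparison of the two self-testing arms is not necessarily unmasked. Blinding remains achievable for testing frequency, reported status and the six secondary outcomes if these are analysed from a file without the arm-specific fields.

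This rests on two assumptions: that the outcomes not described as arm-specific are collected in the same way in all arms, and that the analyst holds neither the SMS logs nor the site-to-arm key. If the second fails, the arm 1 versus arm 2 comparison is unmasked too.

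The correction should be made. It affects how far readers can trust the control comparisons, but it does not show that any estimate is wrong.

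**What to change.** Limit the blinding sentence to named outcomes and stages.

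1. Release first a file with coded groups, coded cluster identifiers, baseline covariates and only the outcomes measured in all arms: last HIV test and testing uptake, reported HIV status, and the six secondary outcomes. Leave out settlement names and all kit, linkage, buy-back and SMS fields. The site-to-arm key stays with someone other than the analyst.
2. The analyst fixes and dates the code and the covariate set on this file.
3. Only then release the arm-specific data and the key.
4. State that the kit and linkage analyses are not blinded as to self-testing versus control. Arm 1 versus arm 2 may stay coded for them.

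If the release is not staged, withdraw the blinding claim for the control comparisons in the protocol and in the trial report.

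The cost is one extra data extract, a few lines of text and a less favourable blinding statement. Because buy-back comes after Time 3 in any case, the two-step release fits the timetable.
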